##### LEAP

LEAP is a semi-structured, problem-oriented group CBT, with psychoeducation specifically focusing on physical activity, behavioral experiments, and cognitive activities. The overarching aim for LEAP is to promote “healthy” exercise. Specific aims are to educate patients about the maintenance of CE, promote insight into factors affecting beliefs and behaviors toward exercise, introduce skills to help challenge maladaptive beliefs and behaviors, introduce adaptive emotion coping strategies, and prevent relapse. Each group contains 4–8 participants. The program consists of 1 individual session (Session 0) and 8 one-hour group sessions over four consecutive weeks. Sessions are preceded by homework tasks. Groups will be held at the treatment units. Two therapists at each treatment unit and three additional therapists from the research group (two acting as supervisors) have been trained in LEAP by the project coordinators and [name] (CM) and clinical psychologist [name] (TC).

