#### Sample size

Based on pilot data and power analysis with beta = .80, alpha = .05, effect size f = .25 and an estimated correlation between pre- and post-measures of .50, a total of 98 patients are required: 49 patients receiving LEAP and 49 controls. With an estimated drop-out rate of 30%, we will enroll 128 participants (64/arm). As there is a minimum of 4 participants in a LEAP group, length of time between initial assessment and first session of LEAP will vary for patients. This variation will need to be considered a covariate.

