#### Data management

*Personal data* (name, contact details) needed for study informing are stored locally at participating units in secure research registries. It is transferred regularly to project managers by phone and entered into a registry. *Medical record data* are transferred to project managers by phone, matched to the correct patient ID (created within BASS upon study consent) and entered into a separate dataset. *Recruitment and intervention data* (non-sensitive personal data (age, gender) for declining participants; intervention related process data) are stored locally at participating units in secure research registries and transferred to project managers after project termination. *Survey, interview, and assessment related data* are stored securely within BASS during the project time; only the project managers and BASS Data Base Administrator (DBA) have access to the database and activity within BASS is logged. After project completion, data will be exported into a separate dataset excluding personal data and deleted in BASS. *Overall project management data* are entered into a research registry at Karolinska Institute. Here, number of participants in each condition is entered as well as information on number of participants, dates, and LEAP therapists for each intervention group at participating units; no personal data are entered here. *Allocation information* including personal data and group is entered into a dataset by the AI and communicated to research contacts at each unit and the participants by phone. All these registries and datasets are stored on a secure server on Karolinska Institute (P-disc under DATA). After study completion, a pseudonymized master datafile will be compiled and stored on the secure KI server (P). A code key matching social security number and patient ID (retrieved from BASS) will be created and stored securely on an encrypted USB-stick in a fireproof safe separate from other data. All other registries containing personal data are destroyed. After project termination, the master datafile will be stored within the KI system for research documentation (ELN) along with the list of variables and related publications. Long-term storage of data follows the KI Archive Act.

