### Statistical methods

#### Outcomes (methods for analyzing primary and secondary outcomes)

To evaluate the LEAP treatment effect (primary objective) the data will be analysed per protocol and based on intention to treat. The first analysis will include all controls (TAU) and participants that complete the program (LEAP+TAU) and answer the questionnaires. The T3 assessment point will be used for post treatment data unless the participants completed the program before T2. Each continuous outcome measure will be used as a response variable in a linear regression model with group allocation and baseline value as predictors. Logistic regression will be used for categorical outcomes. Additional covariates in the models will include gender, clinic, and time between T1 and first treatment session. Since the removal of drop out and noncompliant subjects in the per protocol analysis may lead to overestimation of the treatment effect, we will also perform the same analysis on the basic of intention to treat. Here all subjects who were randomized to LEAP and answered the questionnaires will be included in the treatment group, independently whether they participated in the LEAP sessions. Assessment points with at least CET and EDE-Q will be included in analyses in relation to the primary outcome. If data is missing on CET and/or EDE-Q, the timepoint will not be considered for analysis. There will be no item level missing data (technically prohibited in BASS). The percentage of patients withdrawing from the program despite the initial intention to participate will be considered as a feasibility marker. To compare proportions of dropout and loss to follow-up within the groups, conventional two-sample Z-tests will be used. To identify prognostic factors associated with a good response to LEAP (secondary objective), the treatment group will be subjected to additional analysis where the outcome of interest is used as response variable in linear or logistic regression model and potential prognostic factors (e.g., BMI, type of ED) are used as predictors. These analyses will include all participants with complete data for each specific model.

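### LEAP is group-delivered in one arm only, yet the stated models and the sample size of 98 assume independent patients; if the within-group ICC is positive, standard errors are understated and power is below 80%

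*Protocol article*

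**What the plan says.** On delivery, the LEAP section of the protocol article describes one individual session followed by eight group sessions, and states: "Each group contains 4–8 participants". The Interventions section gives controls usual care alone. The Recruitment section allows one LEAP group at a time per unit and at most two per semester, so each clinic will run several groups over the trial.

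On analysis, the Statistical methods section says: "Each continuous outcome measure will be used as a response variable in a linear regression model with group allocation and baseline value as predictors". Categorical outcomes get logistic regression. The further covariates are gender, clinic and waiting time to the first session. The section names no random effect, robust variance or other term for LEAP group.

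On size, the Sample size section rests on a "power analysis with beta = .80, alpha = .05, effect size f = .25" and "an estimated correlation between pre- and post-measures of .50", and concludes that "a total of 98 patients are required: 49 patients receiving LEAP and 49 controls". It uses neither an ICC nor a group size. Its one remark on groups is that the minimum group size makes waiting time vary, which is to be handled as a covariate.

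**The concern.** Patients who attend the same LEAP group share sessions, peers and therapists, so their outcomes may be more alike than those of patients in different groups. Controls have no such grouping. This is a partially nested design, and the 64 patients randomised to LEAP would form between 64/8 = 8 and 64/4 = 16 groups.

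Ordinary regression counts these patients as independent. With positive within-group correlation, the mean of the LEAP arm varies more than the model allows. The confidence interval for the LEAP effect is then too narrow, a nominal 5% test rejects too often, and the power calculation is optimistic.

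The clinic covariate does not cure this. It removes average clinic differences common to both arms, but not the similarity among members of one LEAP group within a clinic.

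The Discussion makes national implementation the goal if results are beneficial, so a borderline result with understated uncertainty could matter. This is also not a detail left to a later analysis plan, because the article itself fixes the models and lists their covariates.

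**Working it through.** **Inputs from the protocol article.** f = 0.25; pre–post correlation ρ = 0.50; alpha 0.05, taken as two-sided; power 0.80 (the article labels it beta); 49 per arm (Sample size section). Group size m = 4 to 8 in the LEAP arm only (LEAP section).

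**Assumed.** ICC of 0.01, 0.05 and 0.10 on the residual scale, since the article gives none. Groups are of equal size and the total residual variance is the same in both arms.

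**Step 1: reproduce 98.** For a between-group comparison over two measurements, the noncentrality is λ = f² × N × 2 / (1 + ρ).
- N = 98: λ = 0.0625 × 98 × 2 / 1.5 = 8.17, power 0.808.
- N = 96: power 0.799.

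So 98 is the smallest even total that reaches 80%. A baseline-adjusted comparison agrees. With d = 2f = 0.5 and residual variance 1 − 0.50² = 0.75, the noncentral t gives 49 per arm and power 0.808. Both calculations assume independent patients.

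**Step 2: allow for LEAP groups.** Only the LEAP arm is inflated:
- Design effect: DE = 1 + (m − 1) × ICC.
- True SE / naive SE = √[(1 + DE)/2].
- Actual type I error of the naive test = 2 × [1 − Φ(1.96 / SE ratio)].
- Variance for power = 0.75 × (DE/49 + 1/49), using the noncentral t.

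Example, m = 6 and ICC 0.05:
- DE = 1 + 5 × 0.05 = 1.25.
- SE ratio = √(2.25/2) = 1.061.
- Type I error = 2 × [1 − Φ(1.96/1.061)] = 6.5%.
- Variance = 0.75 × 2.25/49 = 0.0344, so SE = 0.186 and noncentrality = 0.5/0.186 = 2.69. Power is 0.76.

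| ICC | m | DE | SE ratio | Type I error | Power at 49 per arm | Evaluable N for 80% |
|---|---|---|---|---|---|---|
| 0.01 | 4 | 1.03 | 1.007 | 5.2% | 0.80 | 98 |
| 0.01 | 6 | 1.05 | 1.012 | 5.3% | 0.80 | 100 |
| 0.01 | 8 | 1.07 | 1.017 | 5.4% | 0.79 | 100 |
| 0.05 | 4 | 1.15 | 1.037 | 5.9% | 0.78 | 104 |
| 0.05 | 6 | 1.25 | 1.061 | 6.5% | 0.76 | 108 |
| 0.05 | 8 | 1.35 | 1.084 | 7.1% | 0.74 | 114 |
| 0.10 | 4 | 1.30 | 1.072 | 6.8% | 0.75 | 112 |
| 0.10 | 6 | 1.50 | 1.118 | 8.0% | 0.72 | 120 |
| 0.10 | 8 | 1.70 | 1.162 | 9.2% | 0.68 | 130 |

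**Step 3: check by simulation.** The naive baseline-adjusted regression was simulated under no effect with 48 per arm. It rejected in 5.8%, 6.4% and 6.8% of trials at ICC 0.05 (m = 4, 6, 8), and in 6.5%, 7.8% and 9.0% at ICC 0.10. At ICC 0 it rejected in 4.8–5.0%.

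**Step 4: few groups.** The powers above use patient-level degrees of freedom. With 49 LEAP patients in about 6 to 12 groups, Satterthwaite degrees of freedom lower power further. At m = 6 it becomes 0.73 (ICC 0.05) or 0.68 (ICC 0.10).

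**The case against.** The strongest objection is that the documents give no ICC. After adjustment for baseline and clinic it could be close to zero, and at 0.01 nothing of substance changes. This stands. A reader might infer that the standard errors are certainly too small and that type I error certainly exceeds 5%, but the article does not support that; it holds only if the ICC is positive.

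The upper figures are also an extreme. A type I error of 9.2% needs every group at the maximum of eight and the highest assumed ICC. The Recruitment forecast works with four per group, where an ICC of 0.05 gives 5.9% and power 0.78. The relevant m is the number analysed per group, so losses shrink it: a group of six with 30% loss leaves 4.2. In the intention-to-treat analysis, LEAP patients who never attend dilute the clustering further. The per-protocol analysis, which the article lists first, includes only LEAP completers and carries it in full. All of this bears on size, not direction.

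A reader might also infer that patients cannot be linked to their groups, because the project management registry holds "number of participants, dates, and LEAP therapists for each intervention group at participating units; no personal data are entered here". That does not follow. The same Data management section lists intervention process data kept at the units. The planned covariate for time to first session needs each LEAP patient's start date, and only one group runs at a time per unit, so clinic and date would normally identify the group. The article does not show that the link is missing.

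Finally, with about 8 to 16 small groups, a variance component is weakly estimated and may come out at zero. This is a fair reason not to insist on a single model.

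**Conclusion.** The point holds in conditional form. Delivery is partially nested, and both the stated models and the 98 treat patients as independent. For any positive within-group ICC, the standard error of the LEAP effect is understated and power at 98 falls below what was calculated.

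The size rests on assumed ICCs. It is negligible at 0.01 and material from about 0.05, where the standard error is 4–8% too small in ratio terms and 104–114 evaluable patients would be needed for 80% power. At 0.10 the ratio is 1.07–1.16 and the need is 112–130. These figures take the analysed number as 98. Whether the drop-out allowance delivers 98 is a separate question and is not counted here. The treatment estimate remains usable; its stated precision and power are what may be unreliable.

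**What to change.** - Carry each patient's LEAP group identifier into the analysis dataset under the patient ID.
- Continuous outcomes: use a partially nested model (random LEAP-group effect in the LEAP arm only, controls as singletons, small-sample degrees of freedom), or keep the planned regression with a small-sample-corrected cluster-robust variance. Name the choice in advance.
- Binary outcomes: use a matching cluster-robust or random-intercept logistic model, and state whether the odds ratio is marginal (cluster-robust) or conditional (random intercept), since the two differ.
- Sample size section: restate power over an explicit range of ICC and group size.

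The cost is one identifier, a standard alternative model, slightly wider intervals and a less favourable stated power. The Trial status section reports that recruitment had not begun, so at that point the identifier could be collected prospectively.

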#### Participant timeline (Fig. 1)

Participants come to the clinic via clinical or self-referral. Within the first three visits, they are assessed using standardized diagnostic interviews, clinical rating scales, and self-report questionnaires. Eligible patients will be asked if they are interested in study participation by clinicians on participating units. Those who are interested will be contacted and formally recruited by the project manager or assistant. They are provided a link to BASS for study consent and the first assessment battery which can be completed directly. Afterwards, they are allocated to either control or intervention group. All participants continue TAU independent of group allocation; for those in the intervention group, LEAP starts when there are enough allocated patients (> 4 patients). After consent, study timeline is at minimum 182 days (three assessment points 90 days apart). Most participants in the intervention group will complete the LEAP program prior to T2 assessment, but due to variation in patient influx at units, some may instead terminate LEAP prior to T3. Participants are no longer included in the study after completed 6-month assessment (T3).

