##### Self-report and interview data

The project includes three assessment timepoints when participants complete questionnaires: T1, 3-month (T2) and 6-month follow-up (T3). Apart from the medical record data at T1, all measurements are distributed to participants through BASS (see below) after study consent. T1 includes self-reports CET, DERS, DSM-5, and Active-Q; T2 includes all T1 self-reports plus the EDE-Q; T3 includes all T2 self-reports plus the treatment content questionnaire (all) and LEAP feasibility and acceptance questionnaire (intervention group only). At T3, the SEDI is also performed by phone.

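### For CET, EDE-Q and DERS the plan analyses one of two follow-up visits per patient with no fallback; a repeated-measures model is a cheap improvement, mainly against arm-specific loss

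*Protocol article*

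**What the plan says.** The protocol article collects the self-reports twice after baseline. Under Self-report and interview data: "T2 includes all T1 self-reports plus the EDE-Q; T3 includes all T2 self-reports plus the treatment content questionnaire (all" participants). CET, EDE-Q and DERS are therefore available at 3 and at 6 months in both arms.

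The section Outcomes (methods for analyzing primary and secondary outcomes) then picks one of the two visits: "The T3 assessment point will be used for post treatment data unless the participants completed the program before T2". The model is given as: "Each continuous outcome measure will be used as a response variable in a linear regression model with group allocation and baseline value as predictors". Gender, clinic and time from T1 to the first treatment session are added as covariates. There is no visit term and no arm-by-visit term.

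On missing data it says: "If data is missing on CET and/or EDE-Q, the timepoint will not be considered for analysis". The intention-to-treat run repeats the same regression among responders: "Here all subjects who were randomized to LEAP and answered the questionnaires will be included in the treatment group". No fallback to the other visit is described.

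On timing, the Participant timeline section says: "Most participants in the intervention group will complete the LEAP program prior to T2 assessment"; some finish only before T3. The Sample size section plans for 30% drop-out.

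**The concern.** The rule selects a visit for each patient and does not say what happens if that visit is missing and the other is present. The other visit also goes unused when both are present. Three things are at stake.

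- **Patients.** Someone with one usable follow-up assessment can drop out of both the per-protocol and the intention-to-treat regression.
- **Bias.** The trial is open-label, and the Harms section accepts that controls may be disappointed. If leaving between T2 and T3 is related to the T2 score differently in the two arms, a regression on those with T3 is biased. The T2 score is the observed variable that could correct this, and the plan leaves it out.
- **Reporting.** No stated analysis compares the arms at both 3 and 6 months.

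The point covers the CET subscales, EDE-Q scales and DERS total only. SEDI remission and BMI have a single post-baseline reading at T3. The DSM-5 domains are declared binary or categorical, so they fall under the logistic model.

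**Working it through.** **1. The plan's own figure.** Inputs from Sample size: f = 0.25, pre-post correlation 0.50, alpha 0.05 (taken as two-sided), power 0.80.

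- Regression on one post value: λ = f²N/(1−ρ²) = 0.0625 × 98/0.75 = 8.17, df 1 and 95, power 80.8%.
- Repeated-measures ANOVA, between-group effect, two measurements: λ = f²Nm/(1+(m−1)ρ) = 0.0625 × 98 × 2/1.5 = 8.17, power 80.8%.
- The same with three measurements needs only 86.

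So 98 reproduces with one baseline and one post-baseline value, which agrees with the one-visit reading of the analysis. With 30% loss, 128 × 0.70 = 89.6 remain, and power on 90 is about 77%.

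**2. Who contributes under the literal rule.**

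| Patient | Visit the rule reads | Result |
|---|---|---|
| Control, T2 answered, T3 missing | T3 | no value |
| Early LEAP completer, T2 missing, T3 answered | T2 | no value |
| Early LEAP completer, both answered | T2 | enters; T3 unused |
| Control or late LEAP finisher, both answered | T3 | enters; T2 unused |

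**3. Precision of the T3 contrast.** Assumed: 15% lost at T2, 30% by T3, T2–T3 correlation 0.6 or 0.7. From the plan: 64 per arm, baseline correlation 0.50, d = 2f = 0.5.

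- Per arm: 64 × 0.85 = 54.4 at T2 and 64 × 0.70 = 44.8 at T3.
- T3 only: variance 2 × 0.75/44.8 = 0.0335, SE 0.183, z = 0.5/0.183 = 2.73, power Φ(2.73 − 1.96) = 78.0%.
- With T2 in the model, the variance is multiplied by 1 − r² × (54.4 − 44.8)/54.4, where r is the T2–T3 correlation given baseline. r = (0.6 − 0.25)/0.75 = 0.467 gives 0.962. r = (0.7 − 0.25)/0.75 = 0.60 gives 0.936.
- Power becomes 79.6% or 80.6%.

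Simulation (3000 trials per scenario) agrees: 77% rises to 78–80%. With all correlations at 0.5, 45 per arm at T3, and 6, 10 or 19 further patients per arm with T2 only, power moves from 78.2% to 78.7%, 79.0% or 79.5%.

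**4. Bias with no true effect.** Loss between T2 and T3 depends on the T2 score with assumed log-odds of 1 per SD. The third column applies the plan's rule with 80% of LEAP patients read at T2 (assumed) and no time trend between the visits.

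| Loss pattern | T3 complete-case regression | Plan's T2/T3 rule | Repeated-measures model |
|---|---|---|---|
| LEAP only, those doing badly leave | 0.05–0.09 SD; type I error up to about 8% | 0.01–0.02 SD | about 0.00 SD, about 5% |
| Opposite directions by arm | 0.11–0.18 SD; type I error 9–16% | 0.06–0.09 SD | about 0.00 SD, about 5% |
| Same in both arms | about 0 (0.006 SD, 5.1%) | not run | about 0 |

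The ranges reflect the two T2–T3 correlations and different calibrations of the loss. Halving the slope to 0.5 with loss in LEAP only gives 0.03 SD and 5.6% at T3.

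**5. If loss depends on the unseen T3 score** (LEAP only): 0.14 SD for the regression and 0.10 SD for the repeated-measures estimate. The bias is reduced but not removed.

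**The case against.** Baseline-adjusted regression on one post value is a recognised method, and the sample size matches it. The full protocol or analysis plan may hold more about missing data. Both statements are true, but the article fixes the visit, the model and the responder set, so changing them is a change of stated method and not the filling of a gap.

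Several stronger readings are tempting and are not supported:

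- **That such patients are expressly excluded.** The article does not say so; it names a visit and gives no alternative. Loss is the literal consequence.
- **That up to half the information is wasted.** Many questionnaires go unused, but the T3 contrast gains only 1 to 3 points of power.
- **That complete-case regression is biased whenever loss depends on the T2 score.** With the same dependence in both arms the null bias is about zero, and a true effect of 0.50 came back as 0.48. The dependence has to differ by arm. The article says controls may be disappointed; it gives no differential loss and no loss at T2.
- **That the T3-only bias figures describe this plan.** Most LEAP patients would be read at T2, and their later loss cannot bias that value. Under the plan's own rule the bias is smaller.
- **That the repeated-measures model is unbiased.** It is so only if loss depends on observed data.
- **That it shows whether the effect lasts after treatment.** Durability is not a stated aim. For those who finish LEAP between T2 and T3, T3 is the first post-treatment value.

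Reading most LEAP patients at 3 months and controls at 6 is a separate and more serious matter. Reading both arms at T3 would cure that and would still leave T2-only patients out.

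**Conclusion.** The point holds as a cheap improvement for the continuous outcomes measured at both visits. The stated analysis uses one visit per patient without a fallback, so some patients with a usable follow-up contribute nothing and early completers' 6-month scores are not analysed.

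The cost in precision is small. The case for change rests on robustness: false effects of roughly 0.05–0.09 SD or 0.11–0.18 SD at T3 under strong arm-specific loss, less under the plan's mixed rule, and near zero if loss is alike in both arms. The loss pattern, the 15% at T2, the T2–T3 correlation and the 80% share are assumptions; the article gives only 30% drop-out and a pre-post correlation of 0.50.

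**What to change.** For the CET subscales, EDE-Q scales and DERS total:

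- Fit a mixed model for repeated measures in all randomised patients with at least one post-baseline value. Use T2 and T3 as responses; arm, visit, arm × visit, baseline, baseline × visit, clinic and gender as terms; and an unstructured covariance.
- Report the LEAP effect at T2 and at T3, and name T3 as the decisive contrast.
- State how time to the first LEAP session is handled. The plan makes it a covariate, but controls have no such session, so it should be neither carried over nor dropped without comment.
- Describe the T2 and T3 results as effects 3 and 6 months from baseline. Claim persistence after treatment only for those who finished LEAP before T2.
- Keep the single-visit regression as a sensitivity analysis.

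The cost is wording and slightly more programming, with no new data. The price is an explicit missing-at-random assumption given baseline and the observed visit, which should be stated.

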### Participants, intervention, and recruitment

#### Eligibility criteria

*Inclusion criteria:* male and female patients, ≥18 years, with AN, BN or OSFED (1. Atypical AN, 2. BN with low frequency and/or limited duration of symptoms, 4. purging disorder/compensatory behaviors after small food amounts), reporting CE at initial assessment (e.g., measured by EDE-Q version 6, item 18, see *Instruments*), and receiving outpatient care at the specialized ED treatment units. As more females than males seek treatment, there will be more females than males in the final sample.

*Exclusion criteria:* inability to communicate in Swedish, psychotic disorder, and/or BMI < 14.

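### The models for the LEAP effect adjust for the wait until the first LEAP session, a post-allocation quantity that controls and LEAP non-attenders do not have

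*Protocol article*

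**What the plan says.** In the protocol article, the statistical methods section (Outcomes) analyses each continuous outcome with a "linear regression model with group allocation and baseline value as predictors", and categorical outcomes with logistic regression. It then adds: "Additional covariates in the models will include gender, clinic, and time between T1 and first treatment session".

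The Sample size section identifies the session. Because a LEAP group needs at least four participants, the "length of time between initial assessment and first session of LEAP will vary for patients", and the article continues: "This variation will need to be considered a covariate".

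Two analysis populations are defined. For per protocol: "The first analysis will include all controls (TAU) and participants that complete the program (LEAP+TAU) and answer the questionnaires". The intention-to-treat run repeats the same analysis and places everyone randomised to LEAP who answered the questionnaires in the treatment group, "independently whether they participated in the LEAP sessions".

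Under Interventions, controls receive treatment as usual (TAU) only. Under Participant timeline, LEAP starts after allocation, once enough patients have been allocated to form a group. The article gives no value or coding of the wait for anyone without a LEAP session.

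**The concern.** A covariate in a between-arm model needs a value for every patient in the comparison. This one is undefined for the whole control arm in both analyses, and also for LEAP non-attenders under intention to treat. Those non-attenders are the patients whom the intention-to-treat run exists to keep.

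The wait is also a consequence of allocation: it comes into being only for patients assigned to LEAP, and only after assignment. It cannot balance the arms as a baseline covariate does.

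The coding therefore decides whether the group coefficient can be estimated at all, what it means, and how precise it is. The covariate sits in every treatment-effect model, so the primary analyses are affected.

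**Working it through.** **Inputs from the article (Sample size):** f = .25 (a standardised difference of 0.5 with two equal arms), alpha .05, pre-post correlation .50, 49 evaluable patients per arm, N = 98, target power .80.

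**Assumed, because the article gives no wait distribution:** k = mean wait / SD of wait in the LEAP arm, taken as 1, 1.5 and 2. The wait is also assumed to explain none of the outcome.

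**1. Reproduce the plan's figure.** For a model with group and baseline value, the noncentrality is f²N/(1 − r²) = 0.0625 × 98 / 0.75 = 8.17. The noncentral F distribution with 1 and 95 df gives power 0.808, and N = 98 is the smallest even total that reaches 80%. The planned sample size is thus reproduced for the model without the wait. In outcome SD units, the standard error of the group coefficient is √(0.75 × 2/49) = 0.175.

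**2. Wait left missing.** Complete-case regression keeps only LEAP attenders, so group is constant and equals the intercept column. The design matrix (intercept, group, baseline, wait) has 4 columns and rank 3. The group effect cannot be estimated.

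**3. Controls coded 0.** With n per arm, residual variance s², and LEAP-arm wait mean m and SD d, the group coefficient is the fitted LEAP value at zero wait minus the control value:

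- Variance with the wait: s²[1/n + 1/n + m²/(n d²)]
- Variance without it: 2s²/n
- Ratio: (2 + k²)/2

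| k (assumed) | Variance ratio | SE ratio | Noncentrality | Power at N = 98 |
|---|---|---|---|---|
| no wait term | 1 | 1 | 8.17 | 0.81 |
| 1 | 1.5 | 1.22 | 5.44 | 0.64 |
| 1.5 | 2.125 | 1.46 | 3.84 | 0.49 |
| 2 | 3.0 | 1.73 | 2.72 | 0.37 |

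A simulation (3,000 runs per setting, 49 per arm, true effect −0.50 SD) used uniform waits of 7–60, 14–120 or 30–150 days, which are also assumptions. These ranges imply k of about 2.2, 2.2 and 2.6. With no true effect of wait, the SE was 0.33 to 0.37 and power 0.27 to 0.34.

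The meaning of the coefficient changes too. If the LEAP effect is assumed to change by 0.004 SD per day of wait, in either direction, the zero-wait coefficient runs from about −0.12 to −0.85, while the effect at the mean wait stays at −0.50.

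**4. Wait centred on the LEAP-arm mean, controls coded 0.** Now m = 0 and the ratio is 1. In the same simulations the coefficient is about −0.50, the SE about 0.175 and power 0.79 to 0.81. Non-attenders still have no observed wait: left missing, they drop out of the intention-to-treat analysis; coded 0, they are treated as having waited the average time.

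**5. Wait removed.** The coefficient is about −0.50, the SE about 0.175 to 0.177 and power 0.79 to 0.81, in line with the planned 80%.

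**The case against.** The strongest reply is that this is a missing coding rule in a condensed article, and that a statistical analysis plan could supply one. Step 4 shows that a harmless coding exists for attenders. It follows that the effect need not become either inestimable or redefined. A reader might infer that it must, but the article prescribes no coding and so does not support that inference.

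The missing-value branch also conflicts with the article's own populations, which keep all controls and, under intention to treat, all LEAP patients who answered the questionnaires. Such an analysis would fail visibly and would not mislead anyone. This stands as a limit on the harm. It also confirms that the covariate and the stated populations cannot both be honoured if the wait is left missing.

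The power losses depend on an assumed k and apply only to uncentred zero-coding. That is correct. They are illustrations, and they do not show that the trial is underpowered.

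Reading the session as the first TAU session does not help: the Sample size section names LEAP, and all participants are already continuing TAU.

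A further inference might be that the binary primary outcomes are compromised because everyone enters with an eating disorder and "reporting CE at initial assessment", so that their baseline value is constant. The article does not support this. It assigns a baseline value only to continuous outcomes, and a constant term would do no harm.

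What remains is more than missing detail. The article itself places in its main models a covariate that is undefined for one whole arm.

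**Conclusion.** The point holds: as written, the adjustment cannot be applied to the populations that the article defines without a coding rule that it does not give. That part rests on the text alone and needs no assumption.

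The size of the harm is conditional. It is total if the wait is left missing. With controls at 0, the SE is 1.22 to 1.73 times larger and power is 64% to 37% instead of about 81%, for an assumed k of 1 to 2 and a wait unrelated to outcome. It is nil for attenders if the wait is centred. The non-attender problem concerns the intention-to-treat analysis only. A claim that the trial will lose this much power, or that a null result would be due to the covariate, would go beyond the documents.

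It should be corrected before analysis, because it touches every treatment-effect model and the correction is simple.

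**What to change.** Remove the wait from all between-arm models, per protocol and intention to treat, linear and logistic. Keep group, gender and clinic, plus the baseline value where the article already specifies it. Amend the covariate sentence in the Sample size section to match. Examine the wait as a secondary analysis within the LEAP arm only, among patients who had a first session.

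If the sponsor prefers to retain the term, state the coding in advance: wait minus the LEAP-arm mean for LEAP attenders, 0 for controls, and an explicit, justified value for non-attenders.

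The cost is wording only; no new data are needed. The downside of removal is that the between-arm model no longer describes how the LEAP effect varies with delay. The within-arm analysis can describe how outcome relates to delay among LEAP patients, but without a randomised comparison.
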